
#### Compliance rate and loss to follow-up

Previous studies from our group in the same study population using comparable criteria for study inclusion and the identical procedure for follow-up (phone calls and questionnaires) yielded a high rate of compliance and a low rate of loss to follow-up, which ranged between 20% [2] in 2003 and 16% in our most recent study [12]. The 16% figure was used in the sample size calculation for the project.

Statistically, appropriate imputation techniques based on the patient´s time course before dropping out will be used to handle missing values as a result of patient drop-out and recently suggested techniques for the prevention of patient drop-out will be observed [41].

#### Randomization

The randomization ratio to the control and intervention group is 1:1. Randomization will be performed by an internet-based tool (Randoulette) [42].

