### Selection of study population

The effect of the Bc*l*l SNP on post-traumatic stress and cortisol signaling has been characterized in patients undergoing CS at our institution who fulfilled the abovementioned criteria [12]. Patients satisfying the entry criteria of our study are in every aspect comparable to patients attending other European CS centers [21]. In addition, our study is a multi-center study with two centers (Klinikum Grosshadern and Herzklinik Augustinum, both in Munich). One can therefore assume that the results of our suggested study can be generalized.

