### Statistical analyses

#### Sample size calculations

In several previous studies in CS patients, we assessed post-traumatic stress using the PTSS-10 instrument that will also be the primary outcome measure in this study. Our preliminary work indicated an 8-point difference on the PTSS-10 scale between homozygous Bc*l*l *G carriers as opposed to non-carriers [12]. This study also showed that the PTSS-10 score did not significantly decrease until six months after surgery. We may assume that the non-trauma-focused control intervention does not change post-traumatic stress levels in homozygous patients and that the difference of 8 points in post-traumatic stress scores between non-carriers and homozygous individuals is clinically meaningful. This assumption is supported by the recent study discussed in the section *Primary endpoint*[26] that showed that even a relatively low PTSS-10 score (>20) in patients one week after ICU therapy and weaning from mechanical ventilation was highly predictive for the later development of PTSD. Based on the results of our pilot study [12], we make the following assumptions: first, the mean PTSS-10 score one year after ICU discharge is 18±8 (mean ±SD) for non-Bc*l*l *G carriers and heterozygous Bc*l*l *G carriers and 25±8 for homozygous Bc*l*l *G carriers each under control intervention. Second, the mean PTSS-10 score one year after ICU discharge is 18 ±8 for all patients under experimental intervention. Both assumptions show a quantitative intervention-SNP interaction. An overall sample size of 252 patients (84 per SNP group) is needed assuming a type I error rate of 5% and a type II error rate of 80% to detect a statistically significant differential treatment effect between the genotype groups. The sample size calculation was performed by Nquery (Statistical Solutions Ltd.,[name]). Further, experience from former studies shows a perioperative mortality of 8% and a loss to follow-up of approximately 20% of patients at the six-month time point [2,12]. Adjustment for a drop-out rate of 30% leads to a total of 120 required patients (120–0.3 × 120 = 84) per SNP group. In our previous study in 126 Western European CS patients from our institution, 43% were non-carriers of the Bc*l*l *G, 43% were heterozygous Bc*l*l *G carriers and 14% were homozygous [12]. This means that we will have to genetically screen approximately 872 patients to detect 120 homozygous individuals eligible for randomization. Genetic screening will also result in the identification of approximately 376 non-carriers and 376 heterozygous individuals. These patients will also be randomly allocated to the control and the targeted intervention group but, to reduce costs, only 120 individuals with each genotype will be randomly selected by choosing every third consecutive heterozygous or non-carrier patient included in the study. Thus, we will have to screen and genotype 872 patients to include 360 patients into the final analyses (Figure 4).

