#### Primary analysis

A two-factorial analysis of variance model will be used that includes the binary factor ‘intervention’ and a trinomial factor ‘genotype’. In a first step, an ‘interaction’ between both factors will be assessed. If this interaction exists in a second step, differential treatment effects will be tested between the three pairs of genotype groups. The global alpha level is guaranteed since the closed testing procedure will be invoked [43]. The primary data analysis set is the intention-to-treat population, which analyzes the data of the patients as they will have been randomized [44].

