#### Sensitivity analyses

The above analysis of variance model will be extended to a linear mixed-effects (LME) model by considering the longitudinal observations per patient (measurements at four time points).

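### The primary ANOVA and its mixed-model extension have no centre term although the trial has two centres, so any centre difference in PTSS-10 stays in the residual of the interaction test

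*Protocol article*

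**What the plan says.** Selection of study population states that "our study is a multi-center study with two centers", both in Munich.

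Primary analysis names the model: "A two-factorial analysis of variance model will be used that includes the binary factor" for intervention, together with a three-level genotype factor. The interaction is assessed first, and then: "If this interaction exists in a second step, differential treatment effects will be tested between the three pairs of genotype groups".

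Sensitivity analyses builds on the same model: "The above analysis of variance model will be extended to a linear mixed-effects (LME) model by considering the longitudinal observations per patient". Nothing else is added to it.

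Randomization has two sentences: "The randomization ratio to the control and intervention group is 1:1", and "Randomization will be performed by an internet-based tool (Randoulette"). It names no strata or blocks, and it does not say that allocation is unrestricted.

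**The concern.** The trial depends on one comparison: whether the intervention effect differs between genotypes. Its precision is set by the residual SD and the cell sizes. If PTSS-10 levels differ between the two hospitals for any reason, a model without centre treats that difference as random error and inflates the residual variance of the interaction test.

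The model is spelled out term by term, so the absence of centre is a stated choice and not merely a detail left open. It matters a little more than usual for two reasons. The planned power is barely above its target. The planning figures are also attributed to a previous study in patients from the investigators' own institution (Sample size calculations). If that was a single hospital, the SD of 8 contains no between-centre variation, while the two-centre trial may.

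**Working it through.** **Inputs (Sample size calculations).** Means are 18 for non-carriers and heterozygotes and 25 for homozygotes, "carriers each under control intervention". Under the intervention, "the mean PTSS-10 score one year after ICU discharge is 18 ±8 for all patients under experimental intervention". The SD is 8 throughout. Alpha is 5%, taken as two-sided. The printed type II error rate of 80% is read as 80% power, the reading that reproduces the stated sample size. The stated requirement is 252 evaluable patients, 84 per genotype, hence 84/2 = 42 per cell under 1:1 allocation.

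**Step 1: reproduce the plan's figure.** The interaction contrast between homozygotes and another genotype is (25 − 18) − (18 − 18) = 7 points. Its standard error with n per cell is SD × √(4/n).

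- n per cell = 4 × [8 × (1.96 + 0.8416)/7]² = 41.0, just above 41, rounded up to 42. This gives 84 per genotype and 252 in total, as stated.
- At n = 42 the standard error is 8 × √(4/42) = 2.469. Power = Φ(7/2.469 − 1.96) = Φ(0.875) = 80.9%.

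**Step 2: leave centre in the residual.** Let the centres differ by d points, with a share p of patients in one of them. Omitting centre adds p(1 − p)d² to the residual variance. The article gives neither d nor p. I assume d = 1 to 4, p = 0.5, and that SD 8 is the within-centre SD. Power is then Φ(7/[√(64 + 0.25d²) × √(4/42)] − 1.96).

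| Assumed shift d | Residual variance | Power, centre omitted | Power, centre in model |
|---|---|---|---|
| 1 | 64.25 | 80.8% | 80.9% |
| 2 | 65.00 | 80.3% | 80.9% |
| 3 | 66.25 | 79.6% | 80.9% |
| 4 | 68.00 | 78.5% | 80.9% |

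**Step 3: vary the assumptions.**

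- Unequal centres (p = 0.3): power with centre omitted is 80.8%, 80.4%, 79.8% and 78.9% for the same shifts.
- A 6-point shift at p = 0.5: 75.6%.
- SD 8 already includes centre variation: the planned 80.9% then holds without the term, and adding it raises power to 81.1%, 81.5%, 82.3% and 83.4% for shifts of 1 to 4 points.
- The 2-df interaction F test, which is the first step of the primary analysis, has more room. It has 83.8% power at 42 per cell, and 83.7%, 83.2%, 82.5% and 81.4% with centre omitted.

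**Step 4: express the loss in patients.** To keep 80% power for the contrast without a centre term, n per cell = 4 × (64 + 0.25d²) × (2.8016/7)². This rounds up to 42, 42, 43 and 44 for d = 1 to 4. Over six cells the loss is nil for 1 or 2 points, 6 patients for 3 points and 12 for 4 points.

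**The case against.** Nothing here is wrong or contradictory. An ANOVA on intervention and genotype is valid in a randomised trial, and the stated sample size reproduces under it. The case for a sizeable centre effect is also not strong. Additional treatments says that all patients follow one strictly standardised protocol, both hospitals are in the same city, and the outcome is a questionnaire sent by post at one year. At shifts of 1 to 3 points the cost is at most about 1.3 power points. A fuller analysis plan, not shown, may already include centre. All of this stands, and it limits the point to a small gain in precision. It does not remove the point, because the article names the model's factors and centre is not among them. Standardised care also does not rule out differences in case mix or local practice.

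A reader might go further and infer that randomisation is unrestricted, so that balance within genotype is left to chance. The article does not support that. It gives a ratio and a tool, and strata and blocks are commonly left to the full protocol. Even if allocation were unrestricted, genotype is a model factor, so chance imbalance would cause no bias. With 84 evaluable patients per genotype, power for the contrast would average 80.5% against 80.9% with exact balance. A 33:51 split among homozygotes, at the edge of the 95% range, would still leave 80.0%.

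**Conclusion.** The point holds as a minor one about precision. The trial has two centres, and neither the primary ANOVA nor its mixed-model extension contains centre, so any centre difference is counted as error in the interaction test. With SD 8 within centre, 42 per cell and equal centres, the power of the contrast falls by about 0.2, 0.6, 1.3 and 2.4 points for assumed shifts of 1, 2, 3 and 4 points. A shift of about 3 points or more takes it below 80%. The article gives no centre difference, so the true size cannot be fixed from it. The loss affects neither the validity of the test nor the sample size, and the point says nothing about how randomisation is restricted.

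**What to change.** Add centre as a fixed main effect to the primary ANOVA, and carry it into the mixed models for the sensitivity analysis and the secondary endpoints. The interaction test and the closed testing steps stay as they are. The cost is one model term and 1 degree of freedom: with 252 evaluable patients and six cells, the residual df go from 246 to 245. The sample size need not change. Trial status describes the study as still under consideration for funding, so the term can be specified before any outcome data exist.

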#### Primary analysis

A two-factorial analysis of variance model will be used that includes the binary factor ‘intervention’ and a trinomial factor ‘genotype’. In a first step, an ‘interaction’ between both factors will be assessed. If this interaction exists in a second step, differential treatment effects will be tested between the three pairs of genotype groups. The global alpha level is guaranteed since the closed testing procedure will be invoked [43]. The primary data analysis set is the intention-to-treat population, which analyzes the data of the patients as they will have been randomized [44].

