**Figure 3 F3:**
[figure not shown]
**Flow chart showing the sequence of events and key points of decision making during the proposed study.** Rounded rectangles indicate tasks to be performed by medical personal (for example, the study physicians). Ovals represent the responsibilities of a study psychologist and his or her team.

After providing written informed consent, blood drawing for genotyping and an evaluation of cognitive ability will follow using the Mini Mental State Examination. Before randomization to either the intervention or the control group, the patients will be asked to complete a set of validated questionnaires to evaluate PTSD stress symptoms, standardized disease-related traumatic memories, depression, health-related quality of life, and current anxiety and pain. Randomization will be followed by the intervention, performed by a psychologist. After surgery, the patients will be admitted to the cardiovascular ICU. While in the ICU (postoperative days 1 to 4), the patients will be evaluated every 8 hours for sedation, delirium, pain and anxiety. Treatment variables will be recorded. One week after discharge from the ICU, the patients will be approached again by the study psychologist and asked to complete the set of questionnaires on traumatic memories from the ICU and post-traumatic stress intensity as well as current anxiety and pain symptoms. Six and 12 months after surgery, the patients will be interviewed by phone and will be sent the set of questionnaires by mail.

The primary efficacy endpoint of the study is a reduction in post**-**traumatic stress measured by questionnaire 12 months after surgery. The primary hypothesis to be tested is that this reduction is more pronounced for high-risk homozygous Bcll SNP carriers compared to the remaining patients.

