### Outcome measures

#### Primary endpoint

We intend to use stress symptom scores determined by the German version of the modified Post-Traumatic Stress Symptom 10 questionnaire (PTSS-10) at one year after CS as the primary endpoint. The PTSS-10 instrument has been repeatedly validated in patients after ICU treatment. In the first validation study performed by our group, we used a double-blind interview technique performed by psychiatrists, according to the Diagnostic and Statistical Manual of Mental Disorders (DSM), third edition criteria, to diagnose PTSD. This validation process demonstrated a high internal consistency (Cronbach’s α = 0.93) and a high test-retest reliability (intraclass correlation coefficient *r* = 0.89) of the instrument. The specificity and sensitivity for diagnosis of PTSD after ICU treatment at a cut-off value of 35 points of the questionnaire were 97.5% and 77%, respectively [25]. The second and more recent validation study was performed by an independent group and according to the newer DSM-IV criteria and demonstrated that a PTSS-10 score of >20 one week after weaning from mechanical ventilation reliably identified patients who were diagnosed with PTSD three months later: sensitivity 100%; specificity 76% with an area under the receiver-operating characteristic curve of 0.91 [26]. The questionnaire has been used in multiple studies investigating traumatic memories and post-traumatic stress after ICU treatment by our [2,25,27-30] and other [15,16,31-34] groups and has also been shown to be sensitive to a pharmacologic intervention aimed at reducing PTSD stress symptoms after CS and ICU therapy in general, namely the use of hydrocortisone [24,33]. When used in patients with coronary artery disease alone, without the stressor of recent CS and at a single time point, the instrument appears to considerably overestimate the incidence of full syndromal PTSD when compared with an interview technique (Structured Interview for DSM Disorders). But even when used under conditions for which the instrument has not been specifically validated, the PTSS-10 was able to adequately quantify the intensity of disease-related stress symptoms [34].

This instrument consists of two parts: *Part A* evaluates four standardized categories of traumatic memory from the ICU and *Part B* quantifies the presence and intensities of 10 PTSD-related symptoms [25]*.*

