##### PTSD-related chronic stress symptoms

The severity and presence of PTSD symptoms is quantified by *Part B* of the questionnaire and evaluates the presence and intensity of ten PTSD-related stress symptoms: sleep disturbance, nightmares, depression, hyperalertness, withdrawal (emotional numbing and inability to care for others), generalized irritability, frequent changes in mood, guilt, fear and avoidance reactions with regard to the ICU, and increased muscle tension. When evaluating these symptoms, the patients are asked to think back over the last few days (‘presently - that means in the past few days - I suffer from…’), and then asked if they had symptoms expressed by statements such as: ‘Jumpiness, I am easily frightened by sudden sounds or sudden movements’ (to evaluate hyperalertness), ‘fear of places and situations which remind me of the intensive care unit’ (to evaluate avoidance reactions), or ‘a bad conscience, blame myself, have guilt feelings’ (to evaluate guilt). Patients rated their symptoms using a scale from 1 (never) to 7 (always). A summary score can then be calculated that ranges from 10 to 70 points, with increasing scores indicating a higher prevalence and intensity of PTSD symptoms.

Traumatic memories and PTSS-10 stress symptom scores will be evaluated before surgery, one week after discharge from the ICU and at six months and one year follow-up time points (Figure 3).

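### The primary two-factor ANOVA leaves out the pre-operative PTSS-10 score, an inexpensive precision gain for a valid analysis that already meets its power target

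*Protocol article*

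**What the plan says.** The Primary analysis section sets the model: "A two-factorial analysis of variance model will be used that includes the binary factor" for intervention and a three-category factor for genotype. Their interaction is tested first, and pairwise differential effects follow if it is present. No covariate is named. The endpoint is the PTSS-10 score "at one year after CS as the primary endpoint" (Primary endpoint).

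The same instrument is scheduled pre-operatively: "Traumatic memories and PTSS-10 stress symptom scores will be evaluated before surgery, one week after discharge from the ICU", and again at six months and one year (PTSD-related chronic stress symptoms). The trial-flow text puts this ahead of allocation: "Before randomization to either the intervention or the control group, the patients will be asked to complete a set of validated questionnaires", and PTSD stress symptoms are among the domains listed.

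Earlier PTSS-10 scores have two other planned uses. The Sensitivity analyses section extends the ANOVA to a linear mixed-effects model over four time points. The sections on loss to follow-up and on secondary endpoints allow missing values to be imputed from a patient's earlier course. Neither puts the pre-operative score into the primary test.

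**The concern.** A score on the primary instrument, taken before randomisation, is usually among the better predictors of the final score. Leaving it out of the model keeps the variance it would explain in the error term.

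That matters more here than in a simple two-arm comparison. The primary estimate is a difference between treatment effects, with about 42 evaluable patients per cell. Homozygotes are also scarce: the sample size section expects to screen about 872 patients to find 120. Precision gained from data already scheduled costs less than precision gained by recruiting.

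**Working it through.** **Inputs (Sample size calculations).** Control means are 18 for non-carriers and heterozygotes and 25 for homozygotes. The intervention mean is 18 for all, and the SD is 8 throughout. The differential effect is therefore 25 − 18 = 7 points. The type I error is 5%, taken as two-sided because that reproduces the stated size. The text gives "a type II error rate of 80% to detect a statistically significant differential treatment effect between the genotype groups", read here as 80% power. The plan has 252 evaluable patients, 84 per genotype, or 42 per cell at 1:1.

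**Reproducing the plan's figure.** Take the contrast of homozygotes against one other genotype, with SE = SD × √(4/n) for n per cell.

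- Required n = 4 × 8² × (1.960 + 0.842)² / 7² = 41.01, rounded up to 42. This gives 84 per genotype and 252 in total, as stated.
- At n = 42, SE = 8 × √(4/42) = 2.47. Power = Φ(7/2.47 − 1.96) = 80.9% (80.6% by noncentral t).

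**The planned first-step test (interaction, 2 df).** The treatment effects by genotype are 0, 0 and 7, with mean 7/3. The sum of squared deviations is 2 × (7/3)² + (14/3)² = 32.67. The noncentrality is 42 × (32.67/2) / 64 = 10.72. With 2 and 246 degrees of freedom, power is 83.8%.

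**Adding the pre-operative score.** With within-cell correlation r between the pre-operative and 12-month scores, residual SD = 8 × √(1 − r²). One degree of freedom is lost (245 remain). The noncentrality becomes 10.72/(1 − r²), and the equivalent unadjusted sample is 252/(1 − r²). The article does not give r, so a range is shown.

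| Assumed r | Residual SD | 2-df interaction power | Pairwise power | Evaluable N for 80% pairwise power | Unadjusted N that 252 is worth |
|---|---|---|---|---|---|
| 0 (plan) | 8.00 | 83.8% | 80.9% | 252 | 252 |
| 0.2 | 7.84 | 85.4% | 82.5% | 240 | about 262 |
| 0.3 | 7.63 | 87.3% | 84.4% | 228 | 277 |
| 0.4 | 7.33 | 89.9% | 87.2% | 210 | 300 |
| 0.5 | 6.93 | 93.0% | 90.6% | 186 | 336 |

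**Covariate or change score.** The trial-flow text describes the endpoint as a reduction, which could suggest analysing change from baseline. If the baseline SD is also 8 (an assumption), the SD of the change is 8 × √(2(1 − r)). At r = 0.3 that is 9.47, and power of the interaction test falls to 69%. A change score is less precise than the plain ANOVA whenever r is below 0.5.

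**The case against.** The strongest reply is that nothing is broken. Intervention is randomised 1:1, the unadjusted interaction test is valid, and the trial was sized on the raw SD of 8 for exactly this analysis. That stands, and it limits the point to efficiency.

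A second reply is that covariates are often settled in a statistical analysis plan, which is not shown, and that a model including two factors need not exclude others. This stands in part. However, the article does specify its primary model, and its sample size reproduces without adjustment, so the natural reading is an unadjusted test.

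A third reply is that r may be low. This also stands. The Exclusion criteria remove patients with pre-existing PTSD, major depression or previous ICU treatment other than brief coronary care stays. Some PTSS-10 content refers to the ICU, which patients have not yet been through. Both could compress the pre-operative score. At r = 0.2 the gain is only 1.6 percentage points on either test.

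A reader might infer that the plan is biased because genotype is not randomised and genotype groups may differ at baseline. The design does not support this: an additive baseline difference between genotypes cancels when treatment effects are compared within genotype. Nor does chance imbalance between arms invalidate the test, since the ANOVA standard error already includes it. It would also be wrong to infer that the longitudinal scores go unused, given the mixed model and the imputation plans.

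**Conclusion.** The point holds as a missed gain in precision. The primary model as stated does not use a pre-randomisation measurement of its own outcome. Over assumed r of 0.2 to 0.5, adjustment adds about 2 to 9 percentage points to the power of the interaction test and about 2 to 10 to that of the pairwise contrast. It is worth about 4% to 33% more patients (1/(1 − r²) − 1).

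These figures rest on the article's own means and SD, 42 evaluable patients per cell, and a linear baseline relation with a common slope. The true r is unknown, and the lower end of the range is plausible. A reader might conclude that the trial is underpowered or its primary result unreliable without adjustment. The figures do not support that, because the unadjusted plan reaches 80.9% pairwise and 83.8% for the 2-df test.

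**What to change.** In the Primary analysis section, define the primary model as an ANCOVA of the 12-month PTSS-10 Part B score on intervention, genotype, their interaction and the pre-operative PTSS-10 score. Keep the unadjusted two-factor ANOVA as a sensitivity analysis. Enter the pre-operative score as a covariate and do not subtract it from the outcome.

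The change is a sentence or two of text and needs no new data collection. It costs one degree of freedom. Because patients are asked to complete the questionnaire and some may not, a rule for missing baseline scores should be set at the same time. The article describes the study as still under consideration for funding and not yet registered, so the covariate can be prespecified before any outcome data exist.

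### The primary analysis contains no test of the stated hypothesis (GG against all remaining patients) and no success rule; power is about 69% to 84% depending on the rule, against about 90% for the direct contrast

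*Protocol article*

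**What the plan says.** - **Hypothesis** (Intervention scheme/trial flow, after Figure 3): the primary hypothesis is that "this reduction is more pronounced for high-risk homozygous Bcll SNP carriers compared to the remaining patients". This is one comparison, GG against CC and CG together.
- **Model** (Primary analysis): a two-way analysis of variance that "includes the binary factor ‘intervention’ and a trinomial factor ‘genotype", so the interaction has 2 degrees of freedom.
- **Second step** (same section): "If this interaction exists in a second step, differential treatment effects will be tested between the three pairs of genotype groups". The pairs are GG–CC, GG–CG and CG–CC.
- **Multiplicity** (same section): "The global alpha level is guaranteed since the closed testing procedure will be invoked".
- **Sample size** (Sample size calculations): for CC and CG patients under control, "the mean PTSS-10 score one year after ICU discharge is 18±8 (mean ±SD"). The mean is 25±8 for "homozygous Bc*l*l *G carriers each under control intervention", and 18±8 for every genotype under the intervention. The result is "An overall sample size of 252 patients (84 per SNP group) is needed". The stated type I error is 5%, and the type II error is printed as 80%. The power target is a differential treatment effect between genotype groups, with no statement of which groups must differ.

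**The concern.** The hypothesis is a single contrast, and the planning assumptions fit it: CC and CG have identical means in both arms. The analysis spends 2 degrees of freedom on the interaction and then splits the comparison group in two. A reader who wants to conclude that GG benefits more than the remaining patients must assemble that conclusion from the interaction and some combination of the GG–CC and GG–CG tests. The protocol does not name the combination.

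Two things are at stake. First, the power for the trial's main question is not defined, because it depends on the unstated rule. Second, mixed results have no agreed reading: the interaction may be significant and GG may differ from one of the other genotypes but not from the other. If the rule is chosen after the data are seen, the confirmatory status of the answer is open to challenge.

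**Working it through.** **Inputs**, all from Sample size calculations except the allocation:
- Treatment effects (control minus intervention): CC 18 − 18 = 0; CG 18 − 18 = 0; GG 25 − 18 = 7.
- SD 8 in every cell.
- 84 evaluable per genotype. With 1:1 allocation (Randomization) this is 42 per cell, 252 in total.
- Type I error 5%. Sidedness is not stated; I take it as two-sided. I read the printed type II error of 80% as 80% power, which the reproduction below supports.

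**Reproducing the 84.** For one pairwise difference between two treatment effects:
- SE = 8 × √(4/42) = 2.47
- 7 / 2.47 = 2.84, and 2.84 − 1.96 = 0.88
- Power is 80.9% (normal) or 80.6% (t, 246 df).

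The matching formula returns 42 per cell, which is 84 per genotype and 252 overall. The stated size is therefore that of a single pairwise comparison without the preceding interaction test.

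**Interaction test (2 df).**
- Variance of one genotype's treatment effect = 2 × 64/42 = 3.05
- Mean effect = 7/3 = 2.33; sum of squared deviations = 2.33² + 2.33² + 4.67² = 32.67
- Noncentrality = 32.67 / 3.05 = 10.72
- Power (F, 2 and 246 df) = 83.8%. For 80%, 77 per genotype would suffice.

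**Direct contrast (1 df): GG effect minus the mean of the CC and CG effects.**
- SE = √(2 × 64/42 + 2 × 64/84) = 8 × √(3/42) = 2.14
- 7 / 2.14 = 3.27, and 3.27 − 1.96 = 1.31
- Power is 90.6% (normal) or 90.3% (t). For 80%, about 63 per genotype would suffice.

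**The two-step procedure**, from 1,000,000 simulated trials at effects 0/0/7. Under closed testing with three groups, each pair is tested at the full 5% once the interaction is significant.

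| What counts as success | Power |
|---|---|
| Interaction significant | 83.8% |
| Interaction and at least one GG pair | 83.8% |
| Interaction and one pre-named GG pair | 76.4% |
| Interaction and both GG pairs | 69.0% |
| Direct GG-versus-rest contrast | 90.3% |

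The gap between the second and fourth rows, 83.8 − 69.0 = 14.8%, is the share of trials in which exactly one GG pair is significant after the interaction. That is about one trial in seven with no rule for reading it.

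**Type I error.** With no effect in any genotype, the simulated chance of any rejection in the two-step procedure is 5.0%.

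**If heterozygotes respond partly** (my assumption; effects 0/3.5/7):
- The contrast becomes 7 − 1.75 = 5.25, and its power falls to 68.8%.
- The interaction test has 71.5%.
- The interaction plus both GG pairs has 27.3%.

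**The case against.** **Power against the protocol's own target.** A reader might infer that the trial has 69% power instead of its planned 80%. The documents do not support that as it stands. The 69% applies only if both GG pairwise tests must be significant, and neither Primary analysis nor Sample size calculations says so. The stated target is a differential effect between genotype groups; the interaction test detects one with 83.8% power, above 80%. What remains is that a significant interaction alone does not show which genotype differs, so it does not by itself answer the stated hypothesis.

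**The three-level factor is defensible.** The abstract's discussion and the Background both describe bringing GG carriers down to the level of non-carriers, and the design includes 120 of each genotype. That suits a study which also wants to place heterozygotes. This stands, and it is a reason to keep the pairwise tests, but as secondary analyses. The formal hypothesis still names the remaining patients as the comparator.

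**A CC–CG difference could drive the interaction.** It could, but the second step tests all three pairs and would show it. With family-wise error held at 5%, this is not a false-positive problem.

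**The contrast is not free.** A reader might infer that it gains power at no cost. It needs no more patients, but its advantage rests on CC and CG responding alike, and the intermediate case above removes its lead over the interaction test.

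**Unequal variances.** The SDs in Gender effects (13.1 and 6.7) might suggest that genotype-specific variances are needed. They come from 6 and 24 women one week after ICU discharge, which is weak evidence about one-year scores, and I make no recommendation from them.

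**The success rule could be in a statistical analysis plan.** It could. But the article itself fixes the hypothesis, the model, the test sequence and the sample size, and these do not match one another.

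**Conclusion.** The concern holds as a mismatch between hypothesis and test. No planned test is GG against the remaining patients, and the protocol does not state which results confirm the hypothesis. Power for the main question therefore lies between about 69% and 84%, depending on the unstated rule, against about 90% for a direct contrast with the same 252 evaluable patients.

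These figures assume a 7-point GG effect, no effect in CC and CG, SD 8 in every cell, 42 evaluable per cell and a two-sided 5% test. The planned tests are valid and error control is sound, so this is a matter of alignment and efficiency. It does not show that the trial is underpowered against its own stated target.

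**What to change.** - **Primary analysis:** pre-specify one test at two-sided 5%: the intervention effect in GG minus the mean of the intervention effects in CC and CG. Equal weights suit the equal group sizes and the equal CC and CG frequencies (43% each) that the protocol reports. State that this test alone decides the primary hypothesis.
- **Secondary analyses:** keep the 2-df interaction and the three pairwise comparisons, so that an intermediate heterozygote effect can still be seen.
- **Sample size calculations:** restate the power as about 90% with 84 evaluable per genotype, conditional on SD 8 in all cells and equal effects in CC and CG. Correct the type II error wording in the same sentence.

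**Cost.** Two sections are reworded, with no extra patients or data. The real downside is that a partial heterozygote response would be addressed only in secondary analysis, and in that case the contrast has no power advantage over the interaction test (about 69% against 71% at assumed effects 0/3.5/7). Trial status describes a study still under consideration for funding, so the change should be easy to make before any outcome data exist.
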